### Participant withdrawal criteria

Subject withdraws voluntarily;Subject experiences serious adverse reactions or serious complications, or a deterioration of the disease occurs in the course of the study, and it is not appropriate to allow continued participation.Subject displays poor compliance with the clinical trial protocols, an unwillingness to continue in the study, or requests to withdraw from the study;Subject is noncompliant with the prescribed treatment, or subject’s incomplete observation data affect the evaluation.

### Treatment of withdrawn participants

The researcher will contact each subject by using home visits, telephone calls, letters, etc., and will record the last treatment time and complete the final assessment; the researcher will try to understand the subject’s reasons for withdrawal from the trial. The researcher will truthfully record these data in the case report.The observation data on all withdrawn participants will be obtained by the subject unit at the end of the trial for collection and statistical analysis.Researchers will record the withdrawal information in detail, will report if there is more than one course of treatment, and will follow-up after 3 months.

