### Treatment of participant discontinuation

After a participant is discontinued, the doctor will provide the appropriate clinical treatment.After the termination of a participant, doctors will investigate the cause and maintain detailed records, retain the observation data of the participant and take the final test results as the final result to analyse both the curative effect and adverse reaction data.

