#### Short-Form McGill Pain Questionnaire

The Short-Form McGill Pain Questionnaire is a high-quality tool used to evaluate neuropathic and nonneuropathic pain conditions [29]. It provides basic information for pain research. The questionnaire will be administered at baseline, the 1st, 2nd, 3rd and 4th weeks of the treatment period, and at the 1-, 2-, 3- and 6-month follow-ups after treatment.

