### rs-fMRI data acquisition

The rs-fMRI scan will be collected with a 3.0 Tesla superconductor (Skyra, Siemens, Erlangen, Germany) in Guang’anmen Hospital. Participants will undergo rs-fMRI scans at baseline and after the 4th week of treatment. Before the scan, participants will be asked to wear earplugs and remove all metal objects from their bodies. Relevant regulations and procedures of the MRI room will be strictly observed. Using foam pads to reduce head movement, participants will be required to remain supine and awake during the entire scan.

Whole cerebral function imaging adopts a T2-weighted echo planar imaging (EPI) sequence for axial scanning, taking the mid-sagittal parallel connection (AC-PC) as the positioning line. Scanning parameters are as follows: number of layers 47, repetition time (TR) = 3000 ms, echo time = 30 ms, layer thickness = 3.0 mm, field of view (FOV) =220 mm × 220 mm, flip angle = 85°, size of voxel = 3.0 mm × 3.0 mm, in-plane resolution = 64 × 64, phase resolution = 100%, and data collection time = 12:30s.

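### Stopping treatment is not separated from leaving the study, so week-4 and follow-up data are not assured for participants who stop needling but would still be assessed

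*Protocol article*

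**What the plan says.** The protocol article, Participant withdrawal criteria, lists as a ground for withdrawal: "Subject is noncompliant with the prescribed treatment". The same item adds data gaps that compromise the evaluation. Clinical worsening counts where "a deterioration of the disease occurs in the course of the study, and it is not appropriate to allow continued participation". Voluntary withdrawal is a further ground.

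For those withdrawn, Treatment of withdrawn participants says: "The researcher will contact each subject by using home visits, telephone calls, letters, etc". The researcher "will record the last treatment time and complete the final assessment". Observation data on all withdrawn participants are to be obtained at the end of the trial and analysed. Researchers also "will report if there is more than one course of treatment, and will follow-up after 3 months".

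Participant discontinuation criteria covers serious adverse events, serious complications and deterioration. For these participants, Treatment of participant discontinuation says that doctors "retain the observation data of the participant and take the final test results as the final result".

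The planned calendar is set elsewhere:
- rs-fMRI data acquisition: "Participants will undergo rs-fMRI scans at baseline and after the 4th week of treatment".
- MNSI, NPSI and LANSS: baseline and week 4.
- BPI and Short-Form McGill: baseline, weekly through week 4, and "at the 1-, 2-, 3- and 6-month follow-ups after treatment".
- SCV and CPT (Primary outcomes; Neurophysiological index): before and after treatment, with no calendar week named.
- Sample size calculation: two resting-state scans per participant, with no exception stated.

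**The concern.** Whether someone receives the treatment and whether their outcome is measured are separate questions. This protocol joins them: failing to follow treatment is a reason to end participation, and no category exists for a participant who is off treatment but on study. Ending participation because data are incomplete can also add to the missing data.

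Stopping may well relate to outcome and to arm. Lack of benefit could drive it under sham, and needle discomfort under electroacupuncture. The Interventions section stops acupuncture for any adverse event without mentioning later assessment, and does not say whether such a stop counts as withdrawal. Several of the common treatment-related events listed under Treatment of adverse events are local effects at the needle site, and only the active needles penetrate the skin. If those who stop are not measured at week 4, the imaging and pain contrasts rest on people who tolerated their allocation, and a scan missed at week 4 cannot be obtained later.

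**Working it through.** **1. The protocol's own figure.** Sample size calculation gives 24 per group and 20% attrition: 24 / (1 − 0.20) = 30 per group, and 30 × 5 = 150. This reproduces. The plan therefore allows for 0.20 × 30 = 6 losses per group, or 24 among the 4 × 30 = 120 treated participants. It does not say how many of these would stop treatment yet remain willing to be assessed.

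**2. What is assured for a participant who stops attending in week 2 but would return.**
- *Week-4 scan.* The second scan is set after the fourth week of treatment, which this person does not reach. The two-scans statement carries no exception, but it describes scans before and after acupuncture and does not mention withdrawn participants. The contact routes listed for withdrawn participants cannot themselves supply an MRI.
- *SCV and CPT.* These are tied to treatment, not to a week, so no date follows for someone off treatment.
- *Week-4 scales.* The final assessment could be held at week 4 or on stopping. Neither its date nor its content is given.
- *BPI and McGill at 1, 2, 3 and 6 months.* Only a follow-up after 3 months is mentioned for withdrawn participants, without content. It could include the month-3 scales. The wording also leaves open whether it applies to everyone or only to those with more than one course.
- *Label.* Serious events, complications and deterioration appear under both withdrawal and discontinuation. Withdrawal brings an assessment and a later follow-up. Discontinuation mentions neither and uses the last test. What is collected can depend on the label the site chooses.

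**3. Illustration of size.** Let f be the fraction of an arm not measured and g the amount, in SD, by which those participants are worse than completers. The full-arm mean is (1 − f) × completer mean + f × withdrawn mean, so the completers look better than the full arm by f × g. The between-arm shift is (f₁ − f₂) × g when g is the same in both arms. The range g = 0.5 to 1.0 is an assumption, as are the unequal losses.
- 20% v 10%: 0.10 × 0.5 = 0.05 SD; 0.10 × 1.0 = 0.10 SD.
- 20% v 0% (extreme): 0.20 × 0.5 = 0.10 SD; 0.20 × 1.0 = 0.20 SD.
- 20% v 20%, equal g: 0.

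For scale, with 24 v 27 measured the standard error of the difference is √(1/24 + 1/27) = 0.28 SD. The 20% v 10% shift is then 0.05/0.28 = 0.18 to 0.10/0.28 = 0.36 standard errors. Its sign depends on which arm loses more.

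**The case against.** A reader might infer that the final assessment happens at the moment of stopping, that the 3-month contact replaces the visit schedule, and that week-4 endpoints are never collected. The text does not say this. The final assessment is undated, the 3-month follow-up is not said to cancel other visits, withdrawn participants' data are to be obtained at the end of the trial, and two scans are stated for each participant. These points stand: collection is unassured, not shown to be cancelled. They do not settle the matter, because the end-of-trial sentence may mean only gathering records that already exist, and it schedules no week-4 visit.

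It is also fair that deterioration leads to withdrawal only where continued participation is judged inappropriate, that incomplete data count only where they affect the evaluation, and that people who leave by choice cannot be kept on any calendar. The illustrative shift uses assumed gaps and unequal losses, whereas the protocol gives one overall attrition figure.

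Clinical data analysis plans to analyse non-compliers as randomised, with what appears to be multiple imputation. That is an analysis rule. It does not decide which visits take place, and it sits uneasily with taking the last test as the final result.

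Finally, an article may leave off-treatment visit procedures to a fuller protocol. The finding rests instead on rules the article does state: noncompliance and incomplete data as withdrawal grounds, and two overlapping sets of handling rules.

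**Conclusion.** The concern holds in a limited form. The protocol makes treatment noncompliance a ground for withdrawal, provides no off-treatment, on-study status, and handles overlapping events under two different rules. Week-4 and follow-up outcomes are therefore not assured for participants who stop treatment but could be assessed. That could bias the week-4 contrast if stopping relates to both outcome and arm.

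The size cannot be derived from the documents. Under the stated assumptions a completers' difference shifts by 0.05 to 0.10 SD with 20% v 10% loss, and by zero with equal loss and an equal gap. This is an inexpensive improvement worth making, not a demonstrated loss of endpoints.

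**What to change.** Revise the withdrawal and discontinuation sections together:
- Define stopping study treatment and leaving the study as separate events.
- Remove treatment noncompliance and incomplete data as reasons to end participation.
- Unless consent is withdrawn, or continued participation is judged inappropriate under the existing criterion, keep randomised participants on the planned calendar counted from randomisation: imaging, SCV, CPT and scales at week 4, then BPI and McGill at 1, 2, 3 and 6 months, whatever number of courses was received.
- Let any exit assessment be added to week 4, not replace it.
- Reconcile the overlapping withdrawal and discontinuation rules so that collection does not depend on the label.

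When treatment must stop, and the judgement on continued participation, are left unchanged. The cost is protocol and possibly consent wording, plus the effort of bringing back participants who have stopped. The visits and scans are already scheduled for all. Trial status expected recruitment to finish by December 2021, so the change helps only participants still in the study.

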### Participant discontinuation criteria

If there are serious adverse events, serious complications, or if subjects exhibit deterioration during the trial, the clinical trial will be suspended in accord with a doctor's judgement.

### Treatment of participant discontinuation

After a participant is discontinued, the doctor will provide the appropriate clinical treatment.After the termination of a participant, doctors will investigate the cause and maintain detailed records, retain the observation data of the participant and take the final test results as the final result to analyse both the curative effect and adverse reaction data.

### Participant elimination criteria

Participants that violate the inclusion and/or exclusion criteria.Participants in erroneous treatment groups.In the exit test, participants documenting the use of banned drugs or treatments and participants with incomplete data collection.

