## Interventions

The acupuncturists providing treatment will be licenced and will have had at least 2 years of clinical experience.

All the acupuncturists who meet this standard will be trained before the trial begins on how to locate acupoints and non-acupoints, how to puncture and how to manipulate needles. Sterile disposable acupuncture needles (length 25–40 mm, diameter 0.25 mm; Hwatuo, Suzhou, China) and SDZ-V electroacupuncture instruments (Hwatuo, Suzhou, China) will be used. Acupuncture will be discontinued if a participant suffers from any adverse events (AEs). During the trial, participants will be prohibited from using treatments other than acupuncture.

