
### Clinical data analysis

According to the study data, the effect indices of the two groups will be calculated and compared to analyse the influence on the prognosis of PDPN. Indices of scales will be analysed by repeating measurement analysis of variance. The main analytical indicators will be the curative effect index and recurrence rate. A *t* test will be used for measurement data with a normal distribution. The Wilcoxon rank sum test will be used for nonnormal distribution; the Pearson chi-square test will be used for counting data. If it is a sequential concatenation table, the CMHX^2^ test will be used.

The measurement data of different treatment groups will be statistically described by the mean ± standard deviation (‾*χ* ± s). Intragroup differences will be assessed using a t-test at baseline; analysis of variance (ANOVA) will be used to compare measurement data at different stages; and SNK will be used for pairwise comparisons. Changes between groups before and after treatment will be analysed by ANOVA. If the data do not fit the above statistical analysis conditions (such as nonnormal), a nonparametric test will be used.

Counting data from different treatment groups are statistically described by frequency (constituent ratio). Changes between groups before and after treatment will be tested using the X2 test (CMHX2 test) or nonparametric test. The analysis of data results from participants not complying with the study protocol will be treated according to statistical analysis with randomization and multiple interpolation.

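### Conflicting rules for overlapping participants: those with incomplete data or protocol departures are eliminated, kept on their last result, or analysed as randomised with imputation, with no order of precedence

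*Protocol article*

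**What the plan says.** Several sections of the protocol article govern the same kinds of participant under different labels.

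- **Participant elimination criteria** gives four grounds: "Participants that violate the inclusion and/or exclusion criteria"; "Participants in erroneous treatment groups"; and, at the exit test, "participants documenting the use of banned drugs or treatments and participants with incomplete data collection". Elimination is not defined and no analysis set is named.
- **Treatment of participant discontinuation** tells doctors to "retain the observation data of the participant and take the final test results as the final result to analyse both the curative effect" as well as the adverse reactions. In effect this carries the last value forward.
- **Clinical data analysis** says that results from participants who depart from the protocol "will be treated according to statistical analysis with randomization and multiple interpolation".
- **Treatment of withdrawn participants** says: "The observation data on all withdrawn participants will be obtained", and sends those data to statistical analysis. The withdrawal criteria just before it include non-compliance with treatment and incomplete data that affect the evaluation.

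**Sample size calculation** needs 24 per group, allows 20% attrition, and recruits 30 per group and 150 in all.

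**The concern.** One participant can meet several of these descriptions at once, and the article does not say which rule then wins. The choice decides who enters the randomised comparison of electroacupuncture with sham.

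Elimination matters most. Wrong treatment group, banned treatment and incomplete data all arise after randomisation, and the last two can depend on how the participant is responding and on which arm they are in. If such people leave the analysis, the remaining groups are no longer the groups that randomisation made comparable. Carrying the last value forward and imputing keep everyone but make different assumptions about the missing outcome, so the same data can give three different estimates.

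**Working it through.** **Step 1. The rules side by side.**

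| Participant | Elimination criteria | Discontinuation or withdrawal sections | Clinical data analysis |
|---|---|---|---|
| Discontinued early, no week-4 data | Eliminated (incomplete data) | Kept on last result | Imputed, if counted as a non-complier |
| Withdrawn because data are incomplete | Eliminated | Data go to analysis | Imputed, if counted as a non-complier |
| Used a banned treatment | Eliminated | Data go to analysis, if withdrawn for poor compliance | Analysed as randomised, with imputation |
| In the wrong treatment group | Eliminated | Not addressed | Analysed as randomised, if counted as a non-complier |

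The first three rows can each receive contradictory instructions. The second needs no inference about overlap: incomplete data is named both as a reason for withdrawal, after which the data are analysed, and as a reason for elimination.

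**Step 2. Timing of the four elimination criteria.** Eligibility violation is a baseline reason. Wrong group, banned treatment and incomplete data are not. Three of four therefore act after randomisation.

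**Step 3. Can the criteria be applied?** No threshold for incomplete is given. The Short-Form McGill questionnaire, on which the sample size rests, has 1 + 4 + 4 = 9 scheduled assessments (baseline, weeks 1 to 4, and months 1, 2, 3 and 6). The reference to the exit test may narrow the criterion, but the article does not say so. For banned treatment, the Interventions section prohibits treatments other than acupuncture, while Table 1 item 4a lists conventional medicine, including analgesia, alongside it. As these stand, who has used a banned treatment cannot be determined.

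**Step 4. The plan's own attrition figure.** 24 / (1 − 0.20) = 30 per group, and 5 × 30 = 150. Both reproduce. (The figure of 24 is taken at face value here.) If all planned attrition met an elimination criterion, 30 × 0.80 = 24 per arm would be analysed, against up to 30 under the other rules.

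**Step 5. Illustration of size within an arm.** Let the 24 retained have mean change m and the 6 removed have mean change r × m. The mean over all 30 is (24m + 6rm)/30, so retained mean ÷ full mean = 30/(24 + 6r).

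- r = 1 (removal unrelated to outcome): 30/30 = 1.00
- r = 0.5: 30/27 = 1.11
- r = 0 (no change in those removed): 30/24 = 1.25

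The documents give no value for r.

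**Step 6. Illustration that the rules disagree.** A simulation of 20,000 trials assumed no true effect, 30 per arm, mean improvement 1 with SD 1, linear change with dropout halfway, and roughly 20% dropout. In one arm poor responders left preferentially; in the other, dropout was random. The mean between-arm difference was 0.00 with complete data, about +0.18 SD after elimination and about +0.07 SD with the last value, favouring the arm that lost its poor responders. Exchanging the arms reverses the sign.

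**The case against.** The strongest reply is that the sections address differently labelled people: withdrawn, discontinued, eliminated and non-compliant. Elimination is undefined, and the sentence on non-compliers is garbled. This is fair. Removal from analysis, and analysis as randomised with multiple imputation, are readings, though the natural ones: the elimination list stands directly after an instruction to retain data, and a per-protocol-only meaning appears nowhere. The sentence on withdrawn participants is also compatible with either carrying forward or imputing. Step 1 shows that the overlap remains.

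A second reply is that a statistical plan, not shown, would define analysis sets, and that statisticians are blinded, the data audit is blind and the database is locked before analysis. These safeguards weaken any suggestion that the rule would be picked to suit the results. They do not say which rule applies, and the conflict is in what the article states rather than in what it leaves out.

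A reader might infer more: that because acupuncture stops on any adverse event, and bleeding under the skin comes from needles that penetrate, removal would fall mainly on the real-needle arm and favour electroacupuncture. The documents do not support this. Stopping treatment is not an elimination criterion, and the sections on withdrawn and discontinued participants call for a final assessment and retained data respectively. Nor is the direction fixed. Use of other treatments could be commoner under sham if real treatment relieves pain better, and eliminating those participants could flatter sham.

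**Conclusion.** The contradiction stands and must be resolved. Overlapping participants are to be eliminated, kept on their last result, or analysed as randomised with imputation, and the article gives no precedence and no analysis set. Followed as written, the elimination list can bias the randomised comparison.

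What can be sized is the number analysed: about 24 of 30 per arm under elimination, if all the planned 20% attrition meets a criterion, against up to 30 otherwise. That 20% is a recruitment allowance, not a forecast of eliminations. The ratio of 1.25 holds only if the six removed had no change, and the simulated differences rest entirely on assumed dropout patterns. Neither estimates the bias in this trial, whose direction and size cannot be determined from the documents.

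**What to change.** Before database lock, name one rule as primary for efficacy: all randomised participants analysed in the arm assigned, all observed data used, and missing values handled by the multiple imputation that Clinical data analysis already appears to intend. A likelihood-based mixed model is an acceptable alternative.

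Then bring the other sections into line:

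- Limit the elimination criteria to defining a per-protocol sensitivity set, and say what counts as incomplete.
- Remove the last-result rule for discontinued participants from the primary efficacy analysis.
- Reconcile the Interventions section with Table 1 item 4a, so that a banned treatment can be identified. Which of the two is right is for the investigators to state.

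The cost is wording, one sensitivity analysis, and an estimate that may be less favourable.

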## Random allocation

Eligible participants will be randomly assigned to three groups: healthy participants (*n* = 30), DM without PDPN participants (*n* = 60) and DM + PDPN participants (*n* = 60). The DM without PDPN and DM + PDPN groups will be randomly divided further into an electroacupuncture group (n = 30) and a sham electroacupuncture group (*n* = 30). We will use a computer program (Random Allocation Software, version 1.0; Msaghaei) [22] to generate this random distribution. The total observation period will be 4 weeks. All three groups will receive 24 sessions of either electroacupuncture or sham electroacupuncture treatment over the 4 weeks (six sessions per week during the treatment period). Before the clinical trial begins, the researchers will provide each participant or his/her legal guardian the details of the clinical study. All participants will be required to provide written informed consent before treatment begins and randomization occurs.

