“Adjust Zang Dredge Meridian” electroacupuncture is a therapy established by our research group under the guidance of Chinese acupuncture and the theory of meridian Zang Fu; it incorporates our understanding of the aetiology and pathogenesis of diabetes and its complications. In the pathogenesis of PDPN, seven acupoints have been identified, including Feishu (BL13), Pishu (BL20), Shenshu (BL23), Hegu (LI4), Zusanli (ST36), Sanyinjiao (SP6) and Taichong (LR3). In contrast to the classic acupuncture method of manual twirling, electroacupuncture is safer and more effective in providing pain relief. The combination of classic and electroacupuncture can achieve the effects of regulating zang-fu organs, nourishing meridians and regulating qi and tong jing zhi tong. Based on earlier studies, our research group has demonstrated in both clinical and animal experiments that “Adjust Zang Dredge Meridian” electroacupuncture can effectively improve pain thresholds and nerve conduction velocities in DPN [18, 19]. Therefore, in applying our previous research to the pathological changes of PDPN, we intend to use fMRI technology to explore the potential effects of acupuncture’s central mechanism in the treatment of PDPN. In this proposed study, the first objective will be to use fMRI technology to reveal the mechanisms of central sensitization in the brain of PDPN patients. The second objective will be to investigate the correlation between peripheral neuropathy, subjective pain and changes in brain function in patients with PDPN. The third objective will be to analyse the neuromodulatory effect of “Adjust Zang Dredge Meridian” electroacupuncture on the central sensitization of the brain in PDPN patients through a controlled study of electroacupuncture and sham electroacupuncture and thus to reveal “Adjust Zang Dredge Meridian” electroacupuncture’s mechanism of action in improving the central sensitization of the brain in PDPN patients.

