## Method

### Study setting/design

This two-armed randomized, sham-controlled clinical trial will be performed at Guang’anmen Hospital (China Academy of Chinese Medical Sciences) and the Affiliated Hospital of Changchun University of Traditional Chinese Medicine. The study protocol has been approved by ethics committees at both participating hospitals. The clinical trial has been approved by the Ethics Committee of the Affiliated Hospital of Changchun University of Traditional Chinese Medicine (CCZYFYLL2018-002) and by Guang’anmen Hospital (China Academy of Chinese Medical Sciences) (2019-070-KY-02), and it was registered with ChiCTR of the Chinese Clinical Trial Registry (NO: ChiCTR1900024109). A flow chart of the trial is shown in Figs. 1 and 2. This study will be reported based on the STandards for Reporting Interventions in Clinical Trials of Acupuncture (STRICTA) checklist [20] and the Standard Protocol Items: Recommendations for Interventional Trials (SPIRIT) checklist [21] (Table 1 and Additional file 1).

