#### Cerebral imaging index

The comprehensive application of multimodal cerebral imaging technology includes the use of rs-fMRI, MRS and DTI based on the BOLD effect. Based on the changes in the functional areas of the cerebral cortex, characteristics of functional connectivity in the whole cerebral cortex, functional connectivity between the cerebral cortex and subcortical nuclei and changes to the white matter and metabolic substances in the cerebral cortex, the objective is to analyse the functional and structural changes of cerebral central sensitization and its neuroimaging mechanism in participants with PDPN.

Based on the above results, participants with PDPN and non-PDPN will undergo multimodal cerebral imaging. The data for both groups will be compared and analysed for changes in cerebral functional areas, characteristics of whole cerebral functional connectivity, abnormal white matter and metabolic changes in the cerebral cortex. The aim of the analysis is to understand the mechanism of electroacupuncture in improving cerebral central sensitization in participants with PDPN.

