### Sample size calculation

This proposed study is an RCT whose primary aim is to evaluate the cerebral imaging mechanism of acupuncture to improve cerebral central sensitization and the clinical effect of acupuncture in patients with PDPN. Acupuncture is a complex intervention that differs from other treatments. Its therapeutic effect is changed if the acupoints are altered. No two-arm, randomized, sham-controlled trial has been conducted on this topic. For this reason, we are using our previous clinical experience to calculate the efficacy of electroacupuncture as an intervention [30, 31]. The proposed sample size of this trial was calculated mainly based on the Short-Form McGill Pain Questionnaire and the assumption that after treatment, the average change reported using this questionnaire would be greater for the experimental group than for the control group. The mean difference was 0.81, with a standard deviation of 0.07. Sample size was calculated using a noninferiority comparison. We set the alpha risk (*α*, type 1 error risk) at 0.025, the beta risk (*β*, type 2 error risk) at 0.2 and the critical value (*Δ*) at − 0.1. Calculating by using SAS [32], the sample size result was 24. Thus, according to this sample size calculation, each group should recruit 24 participants. Allowing for a 20% attrition rate in this study, we plan to recruit 150 participants, with 30 in each of the study groups. Healthy participants will not receive any treatment. Each participant will receive 2 rs-fMRI scans to observe different cerebral activities before and after acupuncture treatment.

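### Healthy volunteers are described as randomised and treated in one section and untreated in another, and the imaging comparison meant to show how electroacupuncture works is set between disease groups instead of between electroacupuncture and sham

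*Protocol article*

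**What the plan says.** All references are to the protocol article.

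- **Random allocation**, on who is randomised: "Eligible participants will be randomly assigned to three groups: healthy participants" (30), DM without PDPN (60) and DM + PDPN (60).
- **Random allocation**, on the second step: "The DM without PDPN and DM + PDPN groups will be randomly divided further into an electroacupuncture group" of 30 and a sham group of 30. The healthy group is not divided.
- **Random allocation**, on treatment: "All three groups will receive 24 sessions of either electroacupuncture or sham electroacupuncture treatment over the 4 weeks".
- **Sample size calculation**, on treatment: "Healthy participants will not receive any treatment". The next sentence gives every participant two resting-state scans, one before and one after acupuncture.
- **Recruitment criteria**: the PDPN, DM-without-PDPN and healthy groups each have their own eligibility list.
- **Background**, objective 3: the effect of EA on central sensitisation in PDPN patients is to be studied "through a controlled study of electroacupuncture and sham electroacupuncture".
- **Cerebral imaging index**, second paragraph: "participants with PDPN and non-PDPN will undergo multimodal cerebral imaging. The data for both groups will be compared and analysed for changes" in brain function, connectivity, white matter and metabolites. The paragraph ends by giving the mechanism of EA in PDPN as the aim of this analysis.
- **Clinical data analysis**: "the effect indices of the two groups will be calculated and compared", with the stated purpose of examining the prognosis of PDPN.
- **Study setting/design**: "This two-armed randomized, sham-controlled clinical trial", although the article describes five cells of 30.

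**The concern.** There are two linked problems.

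First, the article gives two incompatible accounts of the healthy group. In one they are randomised and treated like everyone else; in the other they are untreated. Randomisation to a disease status is not possible, so the first account also presents an observational comparison (healthy, DM, PDPN) as if allocation protected it from confounding.

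Second, the imaging text ties the question of how EA works to a comparison of PDPN with non-PDPN participants. The Abstract names multimodal imaging as the primary outcome measure, so this is the central claim of the study. A difference between those two groups reflects neuropathy and whatever goes with it. If it were reported as evidence on EA, the conclusion would rest on a confounded contrast although a randomised one was available from the same scans.

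**Working it through.** **1. Group arithmetic.** Inputs are from Sample size calculation (24 per group, 20% attrition, 150 in total) and Random allocation (30, 60, 60; six sessions a week for 4 weeks).

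- Inflation for attrition: 24 / (1 − 0.20) = 30 per group.
- Total: 5 × 30 = 150, and 30 + 60 + 60 = 150. The article's total is reproduced.
- Sessions: 6 × 4 = 24. This is also reproduced.

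The 24 per group is taken as given; whether it follows from its stated inputs is a separate matter.

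**2. The two accounts of the healthy group.**

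| Account | Randomised | Treated | Untreated |
|---|---|---|---|
| Random allocation, read literally | 150 | 150 | 0 |
| Sample size calculation, with the EA/sham division in Random allocation | 120 (4 × 30) | 120 | 30 |

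The difference is 30 people, 30/150 = 20% of the study. Random allocation does not agree with itself either: it gives all three groups EA or sham, but divides only the two diabetic groups between EA and sham.

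**3. What can be randomised.** The separate eligibility lists fix whether someone enters as healthy, DM without PDPN or PDPN. Only the second step, EA 30 versus sham 30 within each diabetic group, can be a random allocation.

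**4. What the stated imaging comparison estimates.** Take non-PDPN to mean the DM-without-PDPN group. For any imaging measure, let the mean change under sham be m_P in PDPN and m_N in DM without PDPN, and let the EA effects be t_P and t_N. With a 30:30 split in each group:

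- PDPN group mean: (30·(m_P + t_P) + 30·m_P) / 60 = m_P + t_P/2
- DM-without-PDPN group mean: m_N + t_N/2
- Stated comparison: (m_P − m_N) + (t_P − t_N)/2
- Randomised comparison within PDPN, EA minus sham: (m_P + t_P) − m_P = t_P

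Objective 3 needs t_P. The stated comparison mixes it with m_P − m_N, a disease difference that randomisation does not balance. If EA acts equally in both groups (t_P = t_N), the EA effect cancels completely. If it acts only in PDPN (t_N = 0), half of it appears, still added to the disease difference. If healthy participants were also counted as non-PDPN, the comparison would still be non-randomised.

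**5. Whether another section supplies the right imaging contrast.** The Abstract speaks of changes in each treatment group. Sample size calculation speaks of scans before and after acupuncture. Neuroimaging data analysis covers processing and correlations with clinical measures. None of them names EA versus sham for imaging.

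**The case against.** The strongest reply is that the trial has the right contrast and the article merely words it badly. Objective 3 names EA and sham, Random allocation provides 30 versus 30 within PDPN, and Blinding describes a random division into EA and sham. The paragraph of Neurophysiological index that parallels the imaging one refers to PDPN participants treated with EA and with sham. All of that stands. A reader might infer that the trial has no randomised contrast for objective 3; the documents do not support that. The defect is confined to the imaging comparison.

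A reader might also take the two groups in Clinical data analysis to be EA and sham pooled over both diabetic groups, and infer a loss of power because participants without PDPN have little neuropathic pain to lose. The article does not say this. The sentence continues to the prognosis of PDPN, and the design is labelled two-armed and sham-controlled, so EA versus sham within PDPN is the more natural reading. A power figure for pooling would describe an analysis nobody has stated. It would also concern a pain score, not imaging, and would need assumed standard deviations. None is offered here.

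It can be said too that nobody could carry out a randomisation to disease status, so that wording is only loose. That is fair as to conduct, but the article would still describe an observational comparison as randomised, and the contradiction on treatment remains.

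Finally, model details belong in an analysis plan that is not shown. That is accepted for the choice of model. It does not excuse the imaging text, which states a comparison, and one that does not answer the objective attached to it.

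**Conclusion.** The point holds as a matter of internal consistency, not as a flaw in the underlying design.

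- The statements on treatment of the healthy group contradict each other for 30 of 150 participants and must be reconciled. Which one is correct is not judged here.
- Membership of the healthy, DM and PDPN groups is disease status and is wrongly described as randomised.
- The imaging comparison offered for EA's mechanism is a non-randomised disease contrast that cannot isolate an EA effect and does not match objective 3.

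The algebra assumes the planned equal split within each diabetic group and reads non-PDPN as the DM-without-PDPN group. The conclusion does not depend on any assumed effect size. No numerical bias can be given for the imaging measures, because the article states no expected imaging values.

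**What to change.** 1. **Random allocation:** state that randomisation is only EA versus sham, carried out separately within the PDPN and DM-without-PDPN groups, and that healthy participants are a non-randomised reference group. Bring the Abstract and the two-armed label into line.
2. **Random allocation and Sample size calculation:** reconcile the statements on whether healthy participants are treated, and say what their second scan is for.
3. **Cerebral imaging index:** for objective 3, name the randomised EA-versus-sham comparison of imaging change within PDPN. Adjusting for the baseline scan already collected is preferable, though that detail can sit in the analysis plan. Keep the PDPN, DM and healthy comparisons for objective 1 and label them observational.
4. **Clinical data analysis:** say that the two groups are EA and sham within PDPN.

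The cost is wording only. The scans, the participants and the total of 150 (120 randomised plus 30 reference) stay the same.
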